## Abstract

**Background:**

Acne vulgaris has increased in women over the past 10 years; it currently affects 20–30% of women. The physiopathology of adult female acne is distinguished from that of teenagers essentially by two factors: hormonal and inflammatory. On a therapeutic plan, the four types of systemic treatment approved for female acne include cyclines (leading to bacterial resistance); zinc salts (less effective than cyclines); and antiandrogens (risks of phlebitis). The last alternative is represented by isotretinoin, but its use in women of childbearing potential is discouraged because of the teratogen risks. In this context, spironolactone could represent an interesting alternative. It blocks the 5-alpha-reductase receptors at the sebaceous gland and inhibits luteinizing hormone (LH) production at the pituitary level. It has no isotretinoin constraints and does not lead to bacterial resistance. Currently, very few studies have been performed in a limited number of patients: the studies showed that at low doses (lower than 200 mg/day), spironolactone can be effective against acne. In that context, it is clearly of interest to perform the first double-blind randomized study of spironolactone versus cyclines, which remains the moderate acne reference treatment, and to demonstrate the superiority of spironolactone’s efficacy in order to establish it as an alternative to cyclines.

**Methods:**

Two hundred female patients will be included. They must have acne vulgaris with at least 10 inflammatory lesions and no more than 3 nodules. After randomization, the patients will be treated by spironolactone or doxycycline for 3 months and after placebo. The study will be blind for the first 6 months and open for the last 6 months.

**Discussion:**

The treatment frequently used in female acne is systemic antibiotics with many courses, as it is a chronic inflammatory disease. In the context of the recent World Health Organisation (WHO) revelation about the serious, worldwide threat to public health of antibiotic resistance, this trial could give the physician another alternative in the treatment of adult female acne instead of using isotretinoin, which is more complex to manage.

**Trial registration:**

ClinicalTrials.gov: NCT03334682. Registered on 7 November 2017.

## Administrative information

Note: the numbers in curly brackets in this protocol refer to SPIRIT checklist item numbers. The order of the items has been modified to group similar items (see http://www.equator-network.org/reporting-guidelines/spirit-2013-statement-defining-standard-protocol-items-for-clinical-trials/).

## Introduction

### Background and rationale{6a}

To understand exactly what acne vulgaris is, we must begin below the skin’s surface, deep in the hair follicle. The follicle, which is lined with skin cells, contains sebaceous glands that produce oil (sebum). Normally the skin cells that line the follicle are shed and brought to the skin’s surface by the sebum and are then washed away. However, when the cells stick together instead of shedding, they form a plug or blockage. A clogged pore is a commonly used term for a plugged follicle. Beneath the plug, a sac is formed (known as a microcomedone) that contains dead skin cells and oil. Bacteria (*Cutibacterium acnes*) grow freely in this environment, feeding on the dead skin cells and oil. As the sac continues to grow, either a whitehead (known as a closed comedone), or a blackhead (open comedone) forms. In more serious cases, the sac will become larger, encouraged by the cells that the body sends into the sac to fight the infection. Inflammation will result, and a bump (papule or pustule), painful nodule or cyst will develop.

Though acne becomes less common in adulthood than in adolescence, nearly half of people in their twenties and thirties continue to have it. About 4% continue to have difficulties into their forties [1].

Acne vulgaris has increased in women over the past 10 years. The prevalence is currently 15–50% across different studies [2–4]. Acne in women is now a well-known entity considered as different to adolescent acne [5, 6]. It is reported to most often affect women aged 25 years or older. A recent study isolated two distinct types of clinical presentation: (1) the first is similar to teenager acne, with diffuse acne lesions over the face including hyperseborrhea, retentional lesions (mainly closed comedone) and superficial inflammatory lesions and (2) the second is always mild-to-moderate acne located on the inferior third of the face (mandibular location), mainly with few deep, inflammatory chronic cysts [7].

The physiopathology of adult female acne is characterized mainly by two specific factors:
The hormonal factor suggested by the premenstrual flare-up of acne lesions in more than 60% of women [2, 8] and by the efficacy of anti-androgens and fourth-generation contraception (non-androgenic progestin). The androgen level in blood, previously investigated in women with acne, shows that women with abnormalities are between 7.6% [7] and 86% [9, 10], according to the studies. This strong difference can be explained by the different profiles of female acne included in the trials. Some studies included women with endocrine illnesses associated with hirsutism, irregular cycles and acne. In one study, the serum sex hormone binding globulin (SHBG) values correlated negatively with acne severity, possibly due to an increased level of free testosterone [11]. On the other hand, three other studies did not show any link between androgen level and acne severity [9, 12, 13]. When women with acne with a control population, higher levels of dehydroepiandrosterone (DHEAS) [10, 12], delta-4 androstendione [10], dihydrotestosterone (DHT) [13] and free testosterone [10, 13] have been noted. Last, DHEAS, DHT and insulin-like growth factor-1 (IGF-1) serum levels correlate positively with acne lesion counts in female acne [14]. However, in the majority of women in whom acne is the sole clinical sign (no other clinical sign of hyperandrogenia), no abnormal hormone profiles are present. Two of the main hypotheses discussed today are hypersensitivity of androgen receptors identified in sebocytes and keratinocytes or hyperactivity of enzyme metabolizing androgens in these cells: the term peripheral hyperandrogenia is proposed.Chronic activation of innate immunity of the skin linked to the presence of resistant *C. acnes* strains in the pilosebaceous follicle. In the great majority of women who have had acne for many years, frequent prescriptions of topical antibiotics (erythromycin, clindamycin) induce the development of *C. acnes* and *Staphylococcus* resistant strains.

Four types of systemic treatment are approved in acne [15]:
Cyclines, which can induce modifications of the cutaneous microbiome and bacterial resistance with a risk of non-clinical response [16].Zinc salts, which target only the inflammatory lesions and were shown to be less effective than cyclines [17].Antiandrogens, such as acetate of cyproterone, which are associated with risks of phlebitis, pulmonary embolism, hypertriglyceridemia and hypercholesterolemia.Isotretinoin, which is a teratogenic drug requiring strict use of contraception, with monthly pregnancy testing and testing of cholesterol, triglycerides and liver enzymes. It can also be associated with depression in some patients. In addition, even if the risk of relapse is low after a course of isotretinoin (less than 20%), it has been shown to be higher in women with hyperandrogenia [18]. Thus, even if isotretinoin, by inducing apoptosis of the sebaceous glands, is the most effective drug in acne, its use is sometimes questionable.

Note that the direct cost of acne in the USA is estimated to exceed USD 1 billion per year, with USD 100 million spent on over-the-counter products [19]. Despite this high cost, 81% of women report failures with systemic antibiotics and failures in response to treatment with isotretinoin ranging from 15 to 30% [20].

In this context, spironolactone may represent an interesting alternative. It blocks the 5-alpha-reductase receptors at the sebaceous gland and inhibits luteinizing hormone (LH) production at the pituitary level [21]. It is not subject to the constraints of isotretinoin, does not lead to bacterial resistance and targets peripheral hyperandrogenism.

Currently, 10 randomized controlled trials (RCT) have been performed in a small number of women with acne [22]. Between 10 and 66 female patients with acne were treated by spironolactone. These 10 RCTs included 16 comparisons of spironolactone with placebo or active treatment and all these trials were considered to have a high risk of bias (*inter alia* selection, detection and/or reporting bias). The interest is in the fact that low doses of spironolactone at 50–200 mg per day (with one study using spironolactone at the dose of 100 mg per day but for 16 days per month [23]) appear to induce clinical response in acne. The endpoint varied between studies but was most frequently the lesion count [24–26]. In all the studies published, spironolactone was effective in treating acne lesions located on the face [27] and/or on the back [28–30]. In the largest study published until now, Shaw et al. treated 85 women with spironolactone at 50–100 mg/day either as single-drug therapy or as an adjunctive treatment in an open study. They reported a complete response in treating acne lesions in one third of the cases, a marked improvement in another third, and a partial improvement in the final third of patients [8]. Notably, all these studies were performed in an open setting with no control group. The tolerance of the treatment was excellent. The most frequent adverse events were fatigue and menstrual irregularities, but they were always grade 1 with no need of treatment interruption.

In that context it appears of particular interest to perform the first double-blind randomized study comparing spironolactone with cycline as:
Some open trials indicate that spironolactone is effective in treating female acne, and could represent an interesting alternative to systemic treatments such as antibiotics or isotretinoin.No randomized trials comparing spironolactone with cycline, which remains the reference treatment for moderate acne, have been performedThere is no labelling for acne for spironolactone.

The objective is to demonstrate the superiority of spironolactone’s efficacy in treating adult female acne in order to establish it as an alternative to cycline that could be prescribed by the dermatologist with the advantage of being inexpensive.

### Originality and innovative aspects of the FASCE trial

In spite of numerous scientific references to the efficacy of spironolactone in adult female acne, no RCT has ever been performed to demonstrate its efficacy in comparison with the treatment usually used. Furthermore, the acne treatment frequently used in this indication is an antibiotic treatment, and World Health Organisation (WHO) recently revealed the serious, worldwide threat to public health of antibiotic resistance (WHO First Global on antibiotic resistance - 30 April 2014 [31]).

It is important to find an effective and cheap treatment without using antibiotics. Acne is not lethal but it affects at least 15% of the adult female population and it causes serious problems in daily life with societal impact. This trial could give the dermatologist another alternative to systemic antibiotics before prescribing isotretinoin, for which the management is more complex.

Another original aspect of this study is the use of specific evaluation scales that are more accurate for use in adult female acne. In the past, several grading systems have been described [32]: more than 25 methods of assessing acne severity and more than 19 methods for counting lesions are available. In 1997, for example, Doshi, Zaheer and Stiller devised a global acne grading system (GAGS) [33]. Using this system the face, chest and back are divided into six areas (forehead, each cheek, nose, chin, chest and back) and a factor of 1, 2 or 3 is assigned to each area, based on size. Currently, the commonly used scales for assessing acne in France and in Europe are the Global Evaluation Assessment (GEA) [34] or the *Echelle de Cotation des Lésions d’Acné* (ECLA) [35] as proposed by our team. However, they were designed for treatment of acne in adolescents, and are focused on the lesions located on the face.

As detailed above, women frequently have lesions in the mandibular region, meaning that the use of standard assessment scales could underestimate their lesions. Recently, our new scoring tool, the Adult Female Acne Scoring Tool (AFAST) has been proposed for this purpose [36]. The AFAST scale is composed of the GEA scale to assess acne on the face and a second scale developed to assess acne in the mandibular zone [7]. Thus, the use of currently available scales considering the whole face to assess the severity of acne underestimate the severity of this type of acne, scoring it most of the time as mild and sometimes as moderate. In addition, AFAST modulates results from acne grading on the full face (GEA - score 1) with that of the mandibular and submandibular zone (score 2), which conditions the choice of the most suitable treatment approach:
Score 1: the GEA, as stated, is a validated acne assessment scale [34]. It is based on the global assessment described by Thiboutot et al. [37].Score 2: this score exclusively assesses acne in an area from the left and right mandibular zone to the upper edge of the trunk [36].

The use of this scoring tool will allow us to precisely evaluate the effect of spironolactone in the context of adult female acne.

To conclude, spironolactone has no official labelling for acne, making it difficult for the dermatologist to prescribe it in clinical practice and thus this randomized trial could have an impact on daily practice.

This clinical randomized trial will be stratified by the type of contraception used by the participants. As stated, another option in the arsenal of hormonal treatments is the use of oral contraceptives (OCs), which act largely by suppressing ovarian androgen production. Pills combining oestrogen and progestin are used for acne, as progestin-only and contraceptive implants may exacerbate the condition [38].

Earlier drugs (first and second generation) contain progestogen, derived from the so-called androgenic testosterone (levonorgestrel or norethisterone), with effects close to those of the male hormone and which can therefore aggravate the acne. The progestogen prevails over the estrogen and this pill has a progestational climate and favours acne in women who are subject to it. On the other hand, with third-generation progestogens (gestodene, norgestrel or desogestrel), i.e. those that are not androgenic, the oestrogen asserts itself and the drug climate is oestrogenic, which is desirable in cases of acne, but the effect is more often suspensive, with a relapse after stopping treatment. For fourth-generation drugs, an anti-androgenic progestogen (not just non-androgenic) has been chosen, which neutralizes the androgens. Nevertheless, because of the risk of thrombosis, the French Regulatory Authority (ANSM) advised physicians in December 2012 to systematically favour the second-generation contraceptive pill.

The female patients included in our trial will be women of childbearing potential, except for women who have undergone sterilization surgery or early menopause. They will be included in the study if they use a reliable method of contraception; those who use mechanical contraception or abstinence will not be included.

The women will be stratified on the basis of four strata following the acne effect foreseen by the contraception (some increase acne and others decrease it).:
1st arm: implant, generation I and II OCs, progesterone intrauterine device or other kind of hormonal contraception (vaginal ring, patch, injection).2nd arm: copper intrauterine device (IUD) (hormone-free contraception).3rd arm: generation III and IV OCs.4th arm: no contraception (sterilization surgery or menopause).

### Objectives {7}

The primary objective was to demonstrate the superiority of spironolactone’s efficacy over doxycycline (reference treatment) in adult female acne.

The secondary objective is comparison of the following endpoints in the two study arms:
Safety (clinical and biological) up to 12 months of follow upThe percentage of patients with AFAST score 1 (GEA) at score 0 or 1 at 2, 4, 6, 9 and 12 monthsThe percentage of patients with AFAST score 2 (mandibular) at score 0 or 1 at 2, 4, 6, 9 and 12 monthsComplete remission at 2, 4, 6, 9 and 12 monthsQuality of life at 2, 4, 6, 9 and 12 months

and further:
Comparison of *C. acnes, Malassezia and S. epidermidis, aureus* at baseline (D0) and 4 months in each arm and between the two armsComparison of inflammatory lesions of the face at D0 and 2, 4, 6, 9 and 12 months in each arm and between the two armsComparison of retentional lesions of the face at D0 and 2, 4, 6, 9 and 12 months in each arm and between the two armsComparison of the number of face lesions between D0 and 2, 4, 6, 9 and 12 months in each arm and between the two armsComparison of trunk lesions (factor F2 of ECLA) between D0 and 2, 4, 6, 9 and 12 months in each arm and between the two armsComparison of the percentage of patient relapses between the two arms at month 4 (M4) and month 6 (M6)Comparison of the percentage of patients in the two arms who have reappearance of 10% or more inflammatory lesions at M6Cost-effectiveness analysis (economic efficiency analysis) of spironolactone versus doxycycline at 6 months

### Trial design {8}

Our study is a randomized double-blind trial for the first 6 months (timeline for primary objective), and is an open trial for the last 6 months of follow up. The female patients will be randomized either to the acne routine-care arm, i.e. cycline (doxycycline 100 mg/day for 3 months followed by a placebo for 3 months) or to the experimental drug arm (spironolactone 150 mg/day for 12 months).

Blinding will be removed for all patients after 6 months of evaluation - once the primary endpoint has been measured - whatever the result, to limit the constraints for the patients in the doxycycline arm. If blinding were maintained, patients in the doxycycline arm would have to take a placebo for up to 6 months in addition to the 3 months already taken. The objective of the last 6 months of follow up is to assess the maintenance of each treatment’s efficacy during this time.

## Methods: participants, interventions and outcomes

### Study setting {9}

Patients will be recruited by the dermatology departments of several French reference centres, including study centres in western France belonging to the Dermatological Institute of the Western Region (IDGO), supported by GIRCI GO. The investigation centres are the dermatological departments of the university hospitals of Nantes, Brest, Le Mans, Grenoble and Tours, the regional hospital of La Rochelle and a private dermatologist in Tours.

### Eligibility criteria {10}

It is commonly acknowledged that acne affecting female patients under 20 years of age is considered to be “adolescent female acne”. Since this protocol concerns adult female acne, the recruited patients will be women aged at least 20 years. These patients will have acne vulgaris with at least 10 inflammatory lesions and no more than 3 nodules. The eligibility criteria are shown in Table 1.

**Table 1 Tab1:** Inclusion and non-inclusion criteria of the FASCE trial

Inclusion criteria	Non-inclusion criteria
• Female patient ≥ 20 years old	• Patient affected by active/progressive diseases, as infections including hidradenitis suppurativa, cancers or endocrine syndrome (e.g. polycystic ovary syndrome)*,* Addison’s disease)
• Patient with acne, with at least 10 inflammatory lesions and no more than 3 nodules (GEA score between 2 and 4)	• Patient affected by rosacea (folliculitis)
• Patient who already had one cycline course for her acne treatment with a 3-month* wash out or who never took any cyclines	• Patient with contra-indication to the use of one of the investigational products or auxiliary: ◦ Patient with intolerance or hypersensitivity to cyclines, spironolactone or to any ingredient present in associated benzoyl peroxide gel ◦ Patient with significant impairment of renal excretory function, acute or chronic renal failure, anuria ◦ Patient with life-threatening or very severe hepatic impairment. (grade III or IV)
• Patient having signed an informed consent	• Patient with hyperkalaemia or strongly requiring potassium-sparing diuretics (e.g. amiloride, canrenoate, eplerenone, triamterene) or treated continuously with ACE inhibitors, angiotensin II antagonist, NSAIDs, heparin and molecular-weight heparin, ciclosporin and tacrolimus, or treated with lithium
• Absence of use of oral antibiotics and zinc salts in the last 30 days	• Patient requiring topical isotretinoin or who stopped this drug less than 2 weeks ago
• Absence of use of topical antibiotics in the last 15 days	• Association with potassium salts except in the case of hypokalaemia
• Absence of use of systemic isotretinoin and antiandrogens in the last 6 months (but antiandrogens used as contraceptive are authorized)	• Patient previously treated with spironolactone
• Absence of microphysiotherapy in the last 15 days	• Pregnant woman or likely to become pregnant or nursing and refusing to use an effective contraceptive method
• Women of child-bearing age under contraception for 3 months (oral contraception, implant, IUD or other kind of hormonal contraception)	• Patient participating in another interventional clinical trial
• Patients with social security	• Patient under guardianship or trusteeship

*GEA* Global Evaluation Assessment, *ACE* angiotensin-converting enzyme, *NSAID* non-steroidal anti-inflammatory drug, *IUD* intra-uterine device

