### Relevant concomitant care permitted or prohibited during the trial {11d}

Due to spironolactone, anything that can induce hyperkalaemia is forbidden: potassium-sparing diuretics, potassium supplements and drugs such as ACE inhibitors, angiotensin II antagonists, non-steroidal anti-inflammatory drugs (NSAIDs), heparin and low molecular weight heparin, ciclosporin, tacrolimus and trimethoprim. Lithium is also not recommended in this trial. Concurrent use of lithium and spironolactone may result in increased lithium concentrations and lithium toxicity due to decreased lithium excretion. So, the monitoring of lithium plasmatic concentration will be reinforced.

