### Sample size {14}

For sample size estimation purposes, the targeted difference in the percentage of success is 70% in the experimental arm compared with 50% success in the control arm, indicating a relative increase in success equal to 40%. Assuming a type I error rate of 5% and at least 80% statistical power, the sample size required is at least 91 subjects per group. To take into account the possibility of patients being lost to follow up, 10% (9 subjects) will be added to each group. Finally, approximately 200 subjects will be randomized to the two arms in a 1:1 ratio.

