## Assignment of interventions in a double-blind method

### Who will be blinded {17a}

Our study is a randomized double-blind trial during the first 6 months (timeline for the primary objective), and an open tria during the last 6 months of follow up. The female patients will be randomized either to the acne routine care arm, i.e. cycline (doxycycline 100 mg/day for 3 months followed by a placebo for 3 months) or to the experimental drug arm (spironolactone 150 mg/day for 12 months).

The patients and the investigators and their teams will only be blinded to the treatment assigned during the first 6 months. As Karanicolas et al. pointed out in their article from 2010, their study should have been masked to the biostatisticians until analyses had been performed, to reduce the study bias [45].

Blinding will be removed for all patients after 6 months of evaluation - once the primary endpoint has been measured - whatever the result, to limit the constraints for the patients in the doxycycline arm. If blinding were maintained, patients in the doxycycline arm would have to take a placebo for up to 6 months in addition to the 3 months already taken. The objective of the last 6 months of follow up is to assess the maintenance of the efficacy of each treatment during this time.

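### Table 1 admits a hypokalaemic woman taking potassium salts, while the concomitant-care section forbids potassium supplements without exception

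*Protocol article*

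**What the plan says.** Two sections of the protocol article deal with potassium intake.

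- **Eligibility criteria {10}, Table 1.** One non-inclusion criterion reads "Association with potassium salts except in the case of hypokalaemia". A separate criterion begins "Patient with hyperkalaemia or strongly requiring potassium-sparing diuretics" and goes on to exclude women "treated continuously with ACE inhibitors, angiotensin II antagonist, NSAIDs" and several other drugs that raise potassium.
- **Relevant concomitant care permitted or prohibited during the trial {11d}.** "Due to spironolactone, anything that can induce hyperkalaemia is forbidden: potassium-sparing diuretics, potassium supplements" opens the list of banned treatments. No exception is given for hypokalaemia.

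Three other statements set the context. The experimental arm is described as "experimental drug arm (spironolactone 150 mg/day for 12 months" in Trial design {8}. Allocation is given in Sample size {14}: "approximately 200 subjects will be randomized to the two arms in a 1:1 ratio". On masking, Who will be blinded {17a} states: "The patients and the investigators and their teams will only be blinded to the treatment assigned during the first 6 months".

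**The concern.** The entry rule expressly lets in a woman on a treatment that the on-trial rule expressly bans. The article does not say which rule prevails, and it gives no instruction to stop or wash out the potassium at entry.

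The stake is participant safety and consistent conduct across sites. Spironolactone is the stated reason for the ban, and potassium taken with it is the combination the ban is meant to prevent. Because the site is blind for 6 months, it cannot permit the salts in one arm and stop them in the other. Whichever rule it follows, it departs from the other or leaves the exception without a purpose.

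**Working it through.** No sample size, power or error rate is involved, so the check is a comparison of texts with two small counts.

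**Step 1: follow one woman through both rules.** She is hypokalaemic and takes potassium salts.

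| Point | Rule | Result |
|---|---|---|
| Entry | Table 1, potassium-salts criterion with its exception | Not excluded |
| Entry | Table 1, hyperkalaemia and potassium-sparing drugs criterion | Does not apply; it is silent on low potassium |
| Day 0 onward | Concomitant care {11d} | Her salts are forbidden |

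**Step 2: look for text that reconciles the rules.** The section on discontinuing or modifying interventions {11b} provides for hyperkalaemia only. Outcomes {12} lists ionogram times at 0, 2, 4 and 9 months and has no rule on supplements. The adverse event section {22} reports no raised potassium in earlier acne studies and does not mention supplements. The monitoring committee section {21a} sets a safety review at least yearly. None of these supplies an exception to {11d} or withdraws the one in Table 1.

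**Step 3: is this only the usual stricter rule on trial than at entry?** Section {11d} names 10 drugs or classes: potassium-sparing diuretics, potassium supplements, ACE inhibitors, angiotensin II antagonists, NSAIDs, heparin, low molecular weight heparin, ciclosporin, tacrolimus and trimethoprim. Against Table 1 they divide as follows:

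- Excluded at entry with no exception for a medical indication: potassium-sparing diuretics if strongly required (1), plus seven others if taken continuously (7), giving 1 + 7 = 8.
- Not listed in Table 1: trimethoprim, 1.
- Listed with an express exception: potassium salts, 1.

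Total 8 + 1 + 1 = 10. Potassium salts are the only item for which Table 1 expressly admits a woman on a treatment that {11d} bans.

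**Step 4: what a blinded site can do.**

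- *Follow Table 1 and let her continue the salts.* Under 1:1 allocation her chance of spironolactone 150 mg/day is 1/(1 + 1) = 0.50. The first listed potassium check after baseline is at 2 months.
- *Enrol her and follow {11d}.* She stops her potassium in either arm, including the doxycycline arm, where there is no spironolactone to justify stopping.
- *Decline her.* The exception then has no use.

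**The case against.** The best reply is that the two texts can be read together. Section {11d} has a purpose, to avoid causing hyperkalaemia, and potassium that corrects a low level arguably does not do that. Table 1 is the more specific text on potassium salts, so its exception could be read into the general ban. A condensed article may simply have failed to carry it across. This does not succeed as written, because {11d} does not leave the matter to its purpose: it names potassium supplements as forbidden. Both rules are stated in the article, so this is a conflict and not an omitted detail.

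A second reply is that the sections were never drafted as mirror images. That is true. The strongly-required and continuous-use qualifiers in Table 1 mean that an intermittent NSAID user also passes entry and then meets an unqualified ban. The two sections also treat lithium differently, and the list in {11d} is open-ended, so the count of 10 covers only what is named. The count therefore shows only that potassium salts are the sole item with an express permission at entry; it does not measure harm. Likewise the 50% merely restates the allocation ratio.

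Third, there are safeguards: exclusion of hyperkalaemia at entry, scheduled ionograms, adjustment of spironolactone for hyperkalaemia and the monitoring committee. These reduce the risk to the individual woman and support a low rating, but they do not tell a site which rule to apply.

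Finally, the conflict could be removed the other way, by copying the exception into {11d}. That would be coherent, and it would keep the only allowance the document makes for low potassium. It would also permit potassium with spironolactone under blinding, against the stated principle of {11d}, and would call for an added monitoring rule.

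**Conclusion.** The concern holds, as a minor participant-safety point. Table 1 and section {11d} give opposite instructions for a hypokalaemic woman on potassium salts, and nothing else in the article resolves them.

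Every woman admitted on salts under the exception is in conflict with {11d} at day 0, and on average half of them would be allocated to spironolactone. The article does not say how many such women there would be. None is assumed here, though very few are likely. The conclusion rests on taking the potassium salts of Table 1 and the potassium supplements of {11d} to be the same treatment, and on the absence of any instruction to stop them at entry. The full protocol is not at hand and might settle the matter.

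**What to change.** Delete the hypokalaemia exception from the Table 1 criterion, so that any woman taking potassium salts is not included. She may be reconsidered once her potassium is normal without salts. Leave the ban on potassium supplements in {11d} unchanged. Entry and on-trial rules then agree, and no blinded site admits a woman on a treatment it must at once withdraw or give alongside spironolactone.

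The cost is one phrase removed in an amendment and a note to sites. A few women, a number the document does not give, are deferred or not enrolled, and anyone reconsidered needs a repeat potassium test and a further contact. The change does not address a woman whose potassium falls during the trial; she is already subject to the ban in {11d}, and that stays as it is.
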